### 5 Statistics

***5.1 Sample size justification.*** Data from the Hospital for Tropical Diseases in 2013 showed that 40% of patients with tetanus required ventilation (43 out of 110 in a 6 month period). However an estimated 4–6% of patients did not have generalized tetanus and would be excluded from study entry. Therefore we estimate that 45% of study subjects without intrathecal treatment will require mechanical ventilation in our study. The main comparison of this 2x2 factorial trial is the comparison between subjects receiving intrathecal human antitoxin versus those without intrathecal treatment. To detect an absolute risk reduction for mechanical ventilation due to intrathecal treatment by 17% (from 45% to 28%) with 80% power at the two-sided 5% significance level, 250 subjects are required. To account for some protocol violations and losses to follow-up, the trial will randomize a total of 272 patients (68 in each of the four treatment arms in the 2x2 factorial trial). Should the ventilation rate in the control arm be lower than anticipated, this samples size will also detect a reduction from 40% to 24% with 80% power.

Regarding the secondary endpoint of ICU stay, median (interquartile-range) duration of ICU stay from historic data of 111 tetanus admitted to the Hospital for Tropical Diseases was 13
^4–
22^ days. Based on simulation and these historical data, 272 subjects will provide 88% power to detect a relative reduction in the ICU stay by 25% using the Cox proportional hazards model.

***5.2 Description of statistical methods.*** The primary analysis population for all analysis is the full analysis population containing all randomized patients. Patients will be analyzed according to their randomized arm (intention-to-treat). Analyses for the primary endpoint will be repeated on the per protocol population which excludes the following patients: patients not receiving the randomized intervention and other major violations of inclusion/exclusion criteria or study procedures. 

The primary outcome measure, requirement for mechanical ventilation during ICU stay, will be summarized as x/n (%) in each group and compared between the groups based on a logistic regression model with the two interventions (intrathecal treatment vs. sham procedure, human vs equine intramuscular treatment) as the only covariates without an interaction term. The main comparison is the comparison between intrathecal treatment vs. sham procedure, but the effect of the second randomized intervention will also be summarized as a secondary comparison. As odds ratios from logistic regression are somewhat difficult to interpret for a clinical audience, we will additionally summarize relative risk reductions between the groups based on a binary regression model with a log-link rather than the logit link function used in logistic regression. Interactions between the two interventions are not expected and interaction tests will have low power but we will nevertheless assess potential interactions informally through interaction plots and formally through a likelihood ratio test for an interaction in the logistic regression model. Should the interaction test reach formal significance, we will also perform pair-wise comparisons between the 4 treatment arms.

Potential heterogeneity of the treatment effect will be assessed based on appropriate interaction (likelihood ratio) tests and the following pre-defined sub-grouping variables:

•The Tetanus Severity Score
^27^ (calculated based on information available prior to randomization only) stratified according to tertiles of the observed TSS.•Age: (≤70, 71-80, >80 years)•Pre-existing medical conditions: moderate severe illness, severe illness defined according to ASA physical state scale•Anti-toxin prior to admission

In addition, the primary endpoint will be modelled using a logistic regression model including the two interventions plus additional adjustment for the Tetanus Severity Score, age and pre-existing medical conditions.

Duration of hospital stay, duration of ICU stay, and 240 day mortality will be visualized using Kaplan-Meier curves for all 4 study arms and, additionally, for all patients with and without intrathecal treatment. Formal comparisons of these outcomes (and in-hospital mortality) will be based on Cox regression models with the two interventions as the only covariates using a similar analysis strategy as for the primary outcome described above. 

Other binary endpoints will be analysed in the same way as for the primary outcome. In addition, the rate of new antibiotics prescriptions, ventilator associated pneumonia and other predefined HAI, and the clinical syndrome of autonomic nervous system dysfunction will be modelled with a Poisson-regression model with the log-transformed duration of ICU stay included as an offset.

The cost–effectiveness analysis will be performed from the healthcare provider perspective, thus including direct costs resulting from the implementation of the intervention in the ICU and subsequent costs during the hospital stay, as well as any costs associated with re-admission during the 240 day follow-up. This will include the costs for standard tetanus treatment, the incremental cost of intrathecal human antitoxin administration, and those for any other diagnostics and treatments provided during ICU admission, including time spent on mechanical ventilation.

Prospectively collected data entered in the Case Report Forms from all patients included in the trial will be used for the cost analyses. The unit costs of intrathecal human antitoxin administration and those for mechanical ventilation will be estimated using a detailed micro costing approach. The cost per day of mechanical ventilation will account for the annualized cost of the equipment, maintenance, consumables and staff time.

If the intervention does improve patient survival at a higher cost, we will calculate the incremental cost per ICU survivor. This will be extended to estimating the cost per quality adjusted life year (QALY) gained using the survival data at 240-day-after enrolment follow-up and modelling the anticipated QALYs gained for these patients based on life expectancy and QALYs gained in ICU survivors in the region.

Statistical analysis will be carried out using the latest version of R.

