***3.2 Exclusion criteria***

•Contra-indication to use of human or equine antitoxin•Contra-indication to lumbar puncture•Already receiving mechanical ventilation or expected to require this before intrathecal injection can be given•Pregnancy•Informed consent not obtained

***3.3 Patient identification.*** All patients with generalized tetanus will be identified by doctors working in the Hospital for Tropical Diseases ICU.

***3.4 Informed consent.*** Informed consent will be taken by the attending doctors, all of whom will receive specific training in the study and Good Clinical Practice and will be authorised to take consent by the trial principal investigator (see
Supplementary File 3). These doctors will also assess whether or not the patient has mental capacity to provide informed consent. If the doctor judges that the patient does not have this capacity, they will obtain informed consent from the patient’s representative (usually a relative). It will be made completely and unambiguously clear that the patient (or their representative) is free to refuse to participate in all or any aspect of the trial, at any time and for any reason, without incurring any penalty or affecting their treatment.

The informed consent form will be presented to the participants or representatives detailing no less than: the exact nature of the study; the implications and constraints of the protocol; the known side effects, risks involved and alternatives to taking part. Those who refuse consent will be treated as per the best available standard of care and will not have any study related procedures performed. 

The patient or their representative must personally sign and date two of the latest approved versions of the informed consent form. The study staff will also sign and date the two copies. The patient/representative will receive one copy.

If the patient/representative is illiterate, a witness who is not a member of the study staff will be present during the informed consent discussion. The informed consent form will be read to the patient/representative in the presence of the witness. If the patient/representative agrees to participate, the form will be signed and dated by the witness. If the patient is a minor (defined as < 18 years of age) assent will need to be obtained in addition to parental or guardian consent.

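### The 45% control ventilation rate in section 5.1 does not follow from the inputs given there, which support about 41% or lower; the power consequence is modest and depends on the effect scale

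*Protocol article*

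**What the plan says.** Section 5.1 (Sample size justification) bases the control rate on 2013 data from the study hospital: "40% of patients with tetanus required ventilation (43 out of 110 in a 6 month period"). It adjusts this for one entry criterion: "an estimated 4–6% of patients did not have generalized tetanus and would be excluded from study entry". From these two statements it concludes: "Therefore we estimate that 45% of study subjects without intrathecal treatment will require mechanical ventilation in our study".

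The target is put on the absolute scale, an "absolute risk reduction for mechanical ventilation due to intrathecal treatment by 17% (from 45% to 28"%), and "with 80% power at the two-sided 5% significance level, 250 subjects are required". The number randomized is 272 (136 per side of the intrathecal comparison), the excess over 250 being an allowance for protocol violations and losses. For a control rate below expectation, the section adds that "this samples size will also detect a reduction from 40% to 24% with 80% power".

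Section 3.2 (Exclusion criteria) contains a further exclusion that bears on the control rate and that section 5.1 does not mention: "Already receiving mechanical ventilation or expected to require this before intrathecal injection can be given".

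**The concern.** The control rate is introduced as a deduction, but the two figures before it do not yield 45%. The adjustment made is the one that raises the rate. The exclusion in section 3.2 works the other way, because it removes people who would count as events, and it is left out.

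The control rate and the 17-point target together are the numerical basis for the size of the main comparison. If the rate is really near 41% or below, two things follow. The 40% to 24% scenario, offered as the case where the rate disappoints, is close to the best the data support. And a reader of a null result needs to know which effect the trial had 80% power to detect, which section 5.1 leaves unclear once the control rate moves.

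**Working it through.** **Inputs.** From section 5.1: 43/110 ventilated; 4–6% without generalized tetanus; 45% to 28%; 40% to 24%; 80% power; two-sided 5%; 250 required; 272 randomized. From section 3.2: the exclusion of patients ventilated at or near entry, whose share is not given.

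**Step 1. Reproduce the plan's own figures.** Pooled-variance formula for two proportions, no continuity correction, with p̄ the mean of p1 and p2:

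n per group = [1.96·√(2p̄(1−p̄)) + 0.8416·√(p1(1−p1) + p2(1−p2))]² / (p1−p2)²

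- 45% vs 28%: [1.96·√0.46355 + 0.8416·√0.4491]² / 0.17² = 3.604/0.0289 = 124.7, so 125 per group, total 250. This matches the plan.
- 40% vs 24%: [1.96·√0.4352 + 0.8416·√0.4224]² / 0.16² = 3.385/0.0256 = 132.2, so 133 per group, total 266. With 272 the power is 81.1%, so the stated 80% holds; with 250 it is 77.7%.

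**Step 2. Control rate from the stated inputs.** Let d be the share removed, and assume that none of those removed was ventilated, which gives the highest possible rate: 43/[110(1−d)].

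- d = 0: 43/110 = 39.1%
- d = 4%: 43/105.6 = 40.7%
- d = 5%: 43/104.5 = 41.1%
- d = 6%: 43/103.4 = 41.6%
- from the rounded 40%, d = 6%: 0.40/0.94 = 42.6%
- d needed for 45%: 1 − 43/(0.45 × 110) = 13.1% (11.1% from the rounded 40%)

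**Step 3. The section 3.2 exclusion.** Assumption: a fraction f of the 43 would have been excluded as ventilated at or near entry. With d = 5%, the rate is 43(1−f)/(104.5 − 43f).

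- f = 5%: 40.85/102.35 = 39.9%
- f = 10%: 38.7/100.2 = 38.6%
- f = 20%: 34.4/95.9 = 35.9%
- f = 30%: 30.1/91.6 = 32.9%

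**Step 4. Power at the lower rates.** Power = Φ{[|p1−p2|·√n − 1.96·√(2p̄(1−p̄))] / √(p1(1−p1) + p2(1−p2))}, with n = 125 or 136 per group. The planned 45% to 28% implies a risk ratio of 0.28/0.45 = 0.622 and an odds ratio of (0.28/0.72)/(0.45/0.55) = 0.475. Cells give power with 250 / 272 patients.

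| Control rate | 17 points held | Odds ratio 0.475 held | Risk ratio 0.622 held |
|---|---|---|---|
| 45% (plan) | 80% / 83% | 80% / 83% | 80% / 83% |
| 41% | 82% / 85% | 78% / 81% | 74% / 78% |
| 38.6% (f = 10%) | 84% / 87% | 76% / 80% | 70% / 74% |
| 35.9% (f = 20%) | 86% / 89% | 74% / 78% | 66% / 69% |

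**Step 5. What the fallback implies.** Going from 45% to 40%, the plan moves the target from 17 to 16 points. The implied odds ratio is (0.24/0.76)/(0.40/0.60) = 0.474, almost the 0.475 of the main scenario; the implied risk ratio moves from 0.622 to 0.60. Section 5.1 names no scale for the fallback.

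**The case against.** The strongest reply is that the planned effect is stated as an absolute reduction of 17 points, and at a lower control rate that reduction is easier to detect, not harder: 82% power with 250 and 85% with 272 at 41%. This stands. A reader might infer from the wrong control rate that the stated 80% power is overstated for the planned effect. The documents do not support that, since section 5.1 never states a relative effect for ventilation. What remains is that 17 points from 41% is a 41% relative reduction (0.17/0.41), against 38% in the plan (0.17/0.45), and that the plan's own fallback does not hold 17 points fixed.

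Second, the risk ratio is the least favourable of the three scales, whereas section 5.2 specifies logistic regression for the primary analysis and uses the risk ratio only as an additional summary. On the odds-ratio scale, the power with 272 at 41% is still 81%. This also stands, so the 74% and 78% figures should not be presented as the corrected power of the trial.

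Third, the fallback already covers a rate near 41%. The primary analysis takes all randomized patients, and the endpoint occurs in the ICU, so losses up to day 240 should cost it little and the evaluable number may be close to 272. This largely stands for rates near 40%. It does not help below 40%, and the scenario needs 266 evaluable patients, so it uses all but 6 of the 22 added as an allowance.

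Fourth, the size of the section 3.2 effect is unknown. Section 5.1 does not say when the 43 were ventilated. The fractions in Step 3 are assumptions, and only the direction is clear.

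**Conclusion.** The 45% is not supported by the inputs from which it is said to follow. They give about 41% (40.7–41.6%; 42.6% at the very most from the rounded figure), under the favourable assumption that none of the patients removed was ventilated. The section 3.2 exclusion lowers the rate further, by an amount that the document does not allow one to calculate, to the extent that the historical 43 include such patients.

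The sample size of 250 and both stated powers are correct for the rates entered. Whether power suffers depends on the scale on which the effect is assumed constant. For 17 points it rises. For the odds ratio of 0.475 it is 78% with 250 and 81% with 272 at a 41% control rate. For the risk ratio of 0.62 it is 74% and 78%. On both multiplicative scales it declines further below 40%, where the plan offers no scenario.

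This is a modest point. The derivation of a key design figure is wrong as written and should be corrected, but it does not invalidate the design or call for a larger trial.

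**What to change.** In section 5.1, leaving N at 272:

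- Replace 45% with about 41%, or a lower figure once both exclusions are applied, or give the data that support 45%. A count of how many of the 43 were ventilated at or shortly after admission would settle the second exclusion.
- State on which scale (absolute, odds ratio or risk ratio) the intrathecal effect is assumed constant when the control rate changes.
- Report power at 41% and over a range of lower rates, with the lower rates labelled as assumption.
- Present 40% to 24% as close to the expected case rather than the pessimistic one, and state that it reaches 80% only with at least 266 evaluable patients (77.7% with 250).

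The cost is a revised paragraph and, if the hospital data are still at hand, one look at the historical cases. Design, sample size and analysis are unchanged.

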***1.2 Secondary objectives***

•To determine whether the addition or intrathecal tetanus antitoxin reduces autonomic nervous system dysfunction and length of hospital/ICU stay.•To establish whether the addition of intrathecal tetanus antitoxin in the form of Tetagam-P is safe and cost-effective.•To provide data to inform the recommendation of human rather than equine antitoxin

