***2.2 Secondary End Points***

•Duration of ICU stay•Duration of hospital stay•Duration of mechanical ventilation•In hospital and 240-day mortality and disability•New antibiotic prescription during ICU stay (excluding antibiotics for tetanus or initial entry site infection)•Incidence of Ventilator Associated Pneumonia•Incidence of the clinical syndrome of autonomic nervous system dysfunction•Total dose of benzodiazepines and pipecuronium during hospital stay•Incidence of adverse events

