***3.10 Subsequent assessments.*** Whilst the patient is in ICU, daily treatment interventions (i.e. tracheostomy or mechanical ventilation), doses of predefined drugs, heart rate, blood pressure, respiratory rate, SpO
_2_ and temperature will be recorded. Incidence of predefined hospital-acquired infection and new antibiotic prescriptions will be recorded.

Daily doses of diazepam will continue to be recorded after discharge from ICU until cessation of therapy.

Urinary catecholamines will be measured from a 24-hour collection taken on day 5.

•Criteria for tracheostomy are: laryngeal spasm or sputum retention; or requirement for muscle paralysis and mechanical ventilation due to uncontrolled spasm.

***3.11 Discontinuation of treatment and participation.*** If a patient or the representative, who has given consent on their behalf, chooses to discontinue trial treatment, they should be followed up (providing they are willing) and encouraged to follow the study procedures in lieu of withdrawing from the trial. If they do not wish to remain on trial follow-up, however, their decision will be respected and the patient will be withdrawn from the trial completely. This will be recorded on the OUTCOME Case Report Form (see
Supplementary File 4). The reason for the patient withdrawing should be ascertained wherever possible. Prior to withdrawing completely from the trial, the patient will be invited to have assessments performed as appropriate for the final visit although they would be at liberty to refuse any or all individual components of the assessment.

In addition, the investigator may decide to stop the study intervention if they feel it would not be in the patient’s best interests. Patients will be followed as per protocol. Reasons for stopping the intervention would include, but are not limited to:

•Pregnancy•Ineligibility (either arising during the study or retrospective having been overlooked at screening e.g. an alternative diagnosis to tetanus being confirmed)•Significant non-compliance with treatment regimen or study requirements•Allergic reaction to intramuscular injection•Inability to administer intrathecal antitoxin 

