### 4 Adverse events

Study treatment will be discontinued for all patients displaying anaphylactoid reactions (i.e. if a patient displays anaphylactoid signs after either a test dose or intramuscular dose of antitoxin, then no further antitoxin will be given regardless of treatment allocation). The occurrence of such reactions is rare (<0.5%) and reported to be lower with human than equine antitoxin
^7^. Management of adverse events will follow normal care and current practice guidelines and a standard operating procedure. As these reactions occur irrespective of route of administration, treatment does not require unblinding.

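### Adverse events have only an all-randomised, by-arm analysis, so intrathecal-arm patients who never get the injection dilute the safety comparison; an exposure-based table should sit beside it

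*Protocol article*

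**What the plan says.** **Population.** Protocol section 5.2: "The primary analysis population for all analysis is the full analysis population containing all randomized patients". Patients are grouped by the arm to which they were randomised. The one alternative set has a narrow scope: "Analyses for the primary endpoint will be repeated on the per protocol population".

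**Adverse events as an endpoint.** Section 2.2 lists "Incidence of adverse events" among the secondary end points. Section 5.2 adds: "Other binary endpoints will be analysed in the same way as for the primary outcome". Section 1.2 makes safety an objective: "To establish whether the addition of intrathecal tetanus antitoxin in the form of Tetagam-P is safe and cost-effective".

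**Routes to no injection.** Section 3.11 lists reasons for stopping the study intervention, with follow-up continuing. They include ineligibility, an allergic reaction to the intramuscular injection, and "Inability to administer intrathecal antitoxin". Section 4 says that after an anaphylactoid reaction to the test dose or intramuscular dose "no further antitoxin will be given regardless of treatment allocation", and puts such reactions below 0.5%.

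**Recording.** Under section 4.3, events are recorded from the first dose of study drug until ICU discharge. Section 4.2 lists lumbar puncture events and intramuscular injection events separately.

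**The concern.** Analysis by randomised arm is the usual cautious choice for benefit, because non-receipt of treatment pulls the estimate towards no effect. For harm the same pull is not cautious: it makes the treatment look safer. Under section 3.8 the sham is only a dressing over the lumbar area. An intrathecal-arm patient who never reaches the puncture therefore has the same exposure as a sham patient. Such a patient adds to the intrathecal denominator but cannot contribute a bloody tap, a post-puncture headache or a reaction to intrathecal antitoxin.

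At stake is how faithfully the trial answers its own safety question. The primary endpoint, the sample size and the conduct of the trial are not affected. Nor is this simply a detail left to the analysis plan, because the protocol states one primary population for all analyses and confines its only alternative to the primary endpoint.

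**Working it through.** **The plan's own figure.** The concern rests on no stated figure, but the group size used below does. Section 5.1 gives 45% v 28%, 80% power, two-sided 5% and 250 patients. With pooled variance and no continuity correction,

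n per group = [1.960·√(2 × 0.365 × 0.635) + 0.842·√(0.45 × 0.55 + 0.28 × 0.72)]² / 0.17² = 124.7, so 125 per group and 250 in all.

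This reproduces the plan. With 272 randomised in four arms of 68, the intrathecal comparison is 136 v 136.

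**Dilution.** Let p1 be the event risk if the step is carried out, p0 the risk without it, and f the share of the intrathecal arm in whom it is not carried out. Assume that those patients have risk p0. Then:

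- by-arm risk in the intrathecal group = (1 − f)·p1 + f·p0
- by-arm risk difference = (1 − f)·(p1 − p0)

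**What is known of f.** The only stated rate for any route is below 0.5%, for anaphylactoid reactions: 136 × 0.005 = 0.7, so fewer than one patient. For scale only, the combined allowance for violations and losses in section 5.1 is (272 − 250)/272 = 8.1%. That is not an estimate of f.

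**Illustration.** Event risks of 15% v 5% are assumed (true difference 10 points, relative risk 3.00). The last column is the one-sided 95% upper bound if no serious event is seen, 1 − 0.05^(1/m), with m = 136(1 − f). On all 136 randomised it is 2.18%.

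| f (assumed) | Not injected, of 136 | Difference by arm, points | Relative risk by arm | Power by arm | Power, injected v sham | Zero-event bound, injected |
|---|---|---|---|---|---|---|
| 0.5% | 0.7 | 9.95 | 2.99 | 0.785 | 0.787 | 2.19% |
| 5% | 6.8 | 9.5 | 2.90 | 0.755 | 0.780 | 2.29% |
| 8.1% | 11.0 | 9.2 | 2.84 | 0.733 | 0.774 | 2.37% |
| 10% | 13.6 | 9.0 | 2.80 | 0.718 | 0.770 | 2.42% |
| 20% | 27.2 | 8.0 | 2.60 | 0.636 | 0.750 | 2.72% |

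For comparison, the standard error of the difference with 136 per group is √[(0.15 × 0.85 + 0.05 × 0.95)/136] = 3.6 points.

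**Failed attempts.** A patient in whom a puncture is attempted without antitoxin being delivered has still been exposed to the needle. For puncture events, f should therefore count only patients in whom no attempt was made; for antitoxin events, it should count all who received none intrathecally.

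**Events before the step.** Reactions to the intramuscular dose arise before the intrathecal and sham groups are treated differently. Randomisation balances them, so in expectation they cancel from the risk difference.

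**The case against.** The strongest reply is that the effect is too small to matter. The one stated rate gives a difference of 9.95 instead of 10 points. Other routes are narrowed in advance: section 3.2 excludes patients with a contraindication to lumbar puncture or expected to need ventilation before the injection, and section 8.3 describes operators with more than 500 punctures each. Even at an assumed 10%, the loss of 1.0 point is well inside the standard error of 3.6 points. This stands, and it limits the point to a modest one. It does not remove it, because the direction is known and is the wrong one for a safety claim.

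A second reply is that naming a primary population does not bar a supplementary safety table, that each event is also scored for relatedness, and that the data and safety monitoring board sees unblinded event tables. This also stands in part. However, the protocol names no such supplementary table, so the diluted comparison is the only one it commits to. The article also gives no method specific to adverse events; that they follow the by-arm rule is read from its general wording.

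Two stronger readings are tempting, and the documents support neither:

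- A reader might infer that events between the intramuscular dose and the intrathecal or sham step also push the difference towards none. They are balanced by randomisation. At most they dilute ratios, or mask a later event of the same type where each patient is counted once. The window is short, since section 3.7 aims for all antitoxin within 6 hours of admission while recording runs to ICU discharge.
- A reader might infer that the main analysis should be restricted to completed procedures. That would drop failed punctures, which carry the bleeding, headache and infection risks listed in section 4.2. It would drop them from one side only, because a dressing cannot fail as a puncture can.

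**Conclusion.** The point holds as a gap of principle with a small likely effect. Section 5.2 commits adverse events to the by-arm, all-randomised comparison and gives them no exposure-based companion, while sections 3.11 and 4 foresee uninjected patients in the intrathecal arms. The excess of puncture- and injection-related events is then reported at (1 − f) of its true size.

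The result assumes that uninjected patients carry the sham-group risk, and its size depends wholly on f, which the protocol does not state. The 5–10% range is an assumption and not a forecast. The documents therefore do not show that harm will be materially understated, only that the analysis leans towards no harm if injections are missed. The by-arm table is not wrong and should stay. This is a cheap improvement, not a threat to the trial's conclusions.

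**What to change.** Add to section 5.2 that adverse events for the intrathecal comparison are also reported by procedure received:

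- **Set:** patients in whom the intrathecal or sham step was begun.
- **Exposure:** any attempted lumbar puncture counts as intrathecal exposure, even if no antitoxin was delivered.
- **Events:** lumbar puncture and intrathecal events with onset after the start of that step.
- **Presentation:** beside the all-randomised by-arm table, which is kept, with the number in each arm in whom the step was not begun, so that f is visible.

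The cost is a short addition to the analysis wording and one more table, drawn from the procedure record and event onset times. Sample size, treatment and conduct do not change. The drawback is that the added set is chosen after randomisation and is not fully protected by it: patients may drop out of the intrathecal side for reasons that do not operate in the same way on the sham side. That is why it should accompany the by-arm table and not replace it.
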